## 5. Study outcomes

Outcome definitions and the hierarchical approach to different data sources have been detailed in a supplementary document (S1). This supplemental document may be amended separate to this analysis plan and will be finalised after blinded review of the data with the aim of optimising the validity of outcome definitions. All outcomes for this analysis plan will use one of three denominators as indicated by the following superscript designation:

a Denominator will be all participants whose mothers were randomised in the original trial.

b Denominator will be all participants alive at 28 days of age.

c Denominator will be all participants who consented to this follow-up study with data available for the outcome.

s indicates outcomes for which a separate analysis will be undertaken using only self-reported data (see section 10).

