### **Win Ratio Secondary Outcomes**

- Hierarchical win ratio outcomea: 6 step, unmatched, win ratio hierarchy including time to death after randomisation; time to first major adverse cardiovascular event; diagnosis of diabetes mellitus; number of admissions to hospital with respiratory illness as primary reason for admission; self-reported general health; time in hospital per 10 years alive after 1988
- Components of the win ratio outcome
  - Time to death after randomisationa
  - Time to MACE (excluding cardiovascular death)b
  - Diagnosis of diabetes mellitus (excluding prediabetes)c
  - Number of admissions to hospital with respiratory illness as primary reason for admission (admissions per patient year)b
  - Self-reported general healthc
  - Time in Hospital per 10 years alive after 1988b

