### 4.8. Sensitivity analyses

The following sensitivity analyses will be performed to examine the primary and secondary outcomes:

- Excluding participants for whom there were protocol deviations (per protocol analysis)
- Including current BMI, sex, current socioeconomic status, gestation at birth and birthweight z score (1) in the adjusted analysis

In addition, the following sensitivity analyses will be performed for diabetes outcomes

- Excluding participants for whom the reason for preterm birth was listed as maternal diabetes mellitus
- Excluding participants for whom there was a known family history of diabetes mellitus noted at 30 year follow-up

For the secondary outcome *Hierarchical win ratio outcome* a sensitivity analysis will be performed using time to death after 28 days, excluding those with fetal death or death before 28 days from the analysis.

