### 13. Statistical Analysis

Statistical analysis will be performed for all primary, secondary and tertiary outcomes. Statistical significance will be tested at the 5% significance level using a two-sided test of significance. Analyses will compare the antenatal corticosteroid (betamethasone) group to the control (cortisone acetate) group.

Analyses for binary outcomes will be performed using log binomial regression analysis, reported as relative risk (RR) with 95% confidence intervals.

For continuous outcomes, analysis will be by general linear modelling after assessing model assumptions, using an identity link function and normal distribution.

For time-to-event analyses, a Cox proportional hazards model will be used, reported as a hazards ratio (HR) with 95% confidence intervals. The assumption of proportionality will be verified and if required time dependent functions modelled. Competing risk models will be used if appropriate.

For the hierarchical win-ratio outcome, analysis will follow a stepwise approach in which the six components of the composite outcomes are assessed sequentially (2). The six steps in the hierarchy will start with time to death after randomisation, followed by time to major adverse cardiovascular event, diagnosis of diabetes mellitus, number of admissions to hospital for respiratory illness, self-reported general health and time spent in hospital per 10 years alive. For each step, participants in the treatment and control group will be compared in all possible pairs to determine “wins”, “losses” and “ties”. Pairwise comparisons with ties or missing data at any step will be assessed at the next sequential step in the hierarchy. The analysis will then determine the ratio of the probability of wins and losses for the treatment. The resulting odds ratio will be reported with 95% confidence intervals (2).

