| Proportion with at least one admission for arterial thrombosis/embolism (n/N, %)                                                              |  |  |  |  |  |
| Proportion with at least one admission for peripheral revascularisation procedure (n/N, %)                                                    |  |  |  |  |  |
| Proportion with at least one admission for stroke (n/N, %)                                                                                    |  |  |  |  |  |
| Proportion with at least one admission for heart failure (n/N, %)                                                                             |  |  |  |  |  |
| Win-odds Hierarchical outcome                                                                                                                 |  |  |  |  |  |
| Time to death after randomisation (median, 95% CI)                                                                                            |  |  |  |  |  |
| Time to MACE (excluding cardiovascular death) (median, 95% CI)                                                                                |  |  |  |  |  |
| Diagnosis of diabetes mellitus (excluding prediabetes) (n/N, %)                                                                               |  |  |  |  |  |
| Number of admissions to hospital with respiratory illness as primary reason for admission (admissions per patient year) (mean, SD)            |  |  |  |  |  |
| Self-reported general health (mean, SD)                                                                                                       |  |  |  |  |  |
| Time in Hospital per 10 years alive after 1988 (median, 95% CI)                                                                               |  |  |  |  |  |
| Ischaemic heart disease (n/N, %)                                                                                                              |  |  |  |  |  |
| Stroke (n/N, %)                                                                                                                               |  |  |  |  |  |
| Peripheral vascular disease (n/N, %)                                                                                                          |  |  |  |  |  |

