| Overweight or obesity (n/N, %)                                                                                                                |  |  |  |  |  |
| BMI (continuous) (mean, SD)                                                                                                                   |  |  |  |  |  |
| Death from any cause (n/N, %)                                                                                                                 |  |  |  |  |  |
| Time to death after randomisation (mean, SD)                                                                                                  |  |  |  |  |  |
| Time in Hospital per 10 years alive after 1988 (mean, SD)                                                                                     |  |  |  |  |  |

|                                                                                                                                                                                                                                            |  |  |  |  |  |
|--------------------------------------------------------------------------------------------------------------------------------------------------------------------------------------------------------------------------------------------|--|--|--|--|--|
| Self-reported general health (mean, SD)                                                                                                                                                                                        |  |  |  |  |  |
| Rate of admissions to hospital with respiratory illness as the primary reason for admission/per patient year of followup (mean, SD)                                                                                            |  |  |  |  |  |
| Chronic respiratory illness (Self-reported diagnosis of asthma, self-reported chronic respiratory symptoms, admissions for asthma or chronic obstructive pulmonary disease [COPD] or prescription of pharmaceuticals for asthma or COPD) c |  |  |  |  |  |
| Asthma (n/N, %)                                                                                                                                                                                                                |  |  |  |  |  |

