| Chronic respiratory symptoms (n/N, %)                                                                                                                                                                                          |  |  |  |  |  |
| Proportion with at least one admission for asthma or chronic obstructive pulmonary disease (COPD) (n/N, %)                                                                                                                     |  |  |  |  |  |
| Prescriptions of pharmaceuticals for asthma or COPD (n/N, %)                                                                                                                                                                   |  |  |  |  |  |
| Highest level of educational attainment (n/N, %) 
Tertiary
Secondary
Neither tertiary nor secondary                                                                                                                   |  |  |  |  |  |

Relative risk, Hazard ratio, Mean difference, Hierarchical win ratio outcome: 6 step, unmatched, win ratio hierarchy including time to death after randomisation; time to first major adverse cardiovascular event (MACE); diagnosis of diabetes mellitus; number of admissions to hospital with respiratory illness as primary reason for admission; self-reported general health; time in hospital per 10 years alive after 1988

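### Table 4 gives time to death after randomisation a mean difference and no hazard ratio, contrary to section 13, and does not say what value a living person takes

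*SAP*

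**What the plan says.** Table 4 of the SAP (Appendix 12.2) lists time to death twice. One row is "Time to death after randomisation (median, 95% CI) 4", where footnote 4 is the hierarchical win ratio. The other is "Time to death after randomisation (mean, SD) 3", and the table's key defines that footnote as "3 Mean difference". Neither row carries footnote 2, the hazard ratio, although the rows for age at a cardiovascular event or death do, and the column headings provide for an HR.

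Section 13 states: "For time-to-event analyses, a Cox proportional hazards model will be used, reported as a hazards ratio (HR) with 95% confidence intervals". It does not list which outcomes count as time-to-event. The only model there that produces a mean difference is this one: "For continuous outcomes, analysis will be by general linear modelling after assessing model assumptions, using an identity link function and normal distribution".

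In section 5.2 the outcome appears only among the win-ratio components, as "Time to death after randomisation a". Superscript a is defined in section 5: "Denominator will be all participants whose mothers were randomised in the original trial". The stand-alone mortality outcome in section 5.2 is death from any cause, also with denominator a. Early deaths are removed only in the win-ratio sensitivity analysis of section 4.8, "excluding those with fetal death or death before 28 days from the analysis".

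**The concern.** Time to death is right-censored for everyone still alive. That most of the cohort is alive at about 50 years is not stated in the SAP, but it is a reasonable assumption. A mean and SD need a number for each person, and the plan gives none for survivors. An analyst could average over the dead only, which conditions on the outcome. Or survivors could be entered at their last follow-up, which makes the result depend on length of follow-up as well as on deaths. The two calculations answer different questions and can point in opposite directions.

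The study hypothesis is fewer neonatal deaths without long-term harm. Preventing early deaths and adding late deaths both raise the mean among the dead, so on that reading the row could not separate the hoped-for benefit from the harm that the follow-up looks for.

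**Working it through.** The SAP states no mortality rate, event count or power for this outcome, so there is no figure of its own to reproduce. The inputs below are assumptions, chosen to show how the two readings behave.

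**Inputs.** Early death risk e = 0.15 in both arms, at a mean of 0.1 years. Late death risk l = 0.08 in control and 0.16 with betamethasone, at a mean of L = 35 years. Survivors, where they are entered, take 50 years (the nominal follow-up in section 4.1).

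**Reading A, the dead only.** Mean = (0.1e + L·l) / (e + l).
- Control: (0.015 + 2.80) / 0.23 = 12.2 years.
- Betamethasone: (0.015 + 5.60) / 0.31 = 18.1 years.
- Difference: +5.9 years, for the arm with more deaths.

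**Reading B, everyone randomised, survivors at 50 years.** Mean = 0.1e + L·l + 50(1 - e - l).
- Control: 0.015 + 2.80 + 38.5 = 41.3 years.
- Betamethasone: 0.015 + 5.60 + 34.5 = 40.1 years.
- Difference: -1.2 years, which has the right sign.

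**Row above in Table 4, death from any cause.** 31% against 23%; relative risk 0.31 / 0.23 = 1.35.

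**Range for reading A.**
- With L from 25 to 40 years and the other inputs kept, the difference runs from +4.2 to +6.7 years.
- With early mortality of 2-20% and late mortality of 3-10% doubled, it runs from +2.7 to +6.0 years.
- With no early deaths it is about zero (0 to -0.4 years).

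Reading B gave -0.45 to -1.5 years where late deaths were doubled and early deaths were equal.

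**Precision.** Assume 500 per arm, 10% early deaths at about 0 years in both arms, and late deaths of 5% against 10% spread evenly over 20-50 years. Reading A gives 11.7 against 17.5 years, +5.8 (95% CI +0.5 to +11.2). Reading B gives -0.75 (95% CI -2.65 to +1.15).

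**Early benefit against late harm under reading A.** Starting from the control mean of 12.2 years:
- Early deaths cut from 15% to 10%: (0.010 + 2.80) / 0.18 = 15.6 years.
- Late deaths raised from 8% to 12%: (0.015 + 4.20) / 0.27 = 15.6 years.

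Both show +3.4 years.

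**A single overall measure also blends the two.** If early deaths fall from 15% to 10% while late deaths rise from 5% to 10%, total mortality is 20% in each arm and the risk ratio is 1.00. This is why the fix below separates the two periods.

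**The case against.** A reader might infer that the plan will report late harm as several years of extra survival. The documents do not support that. The reversal needs a mean over the dead only, which the SAP nowhere states and which sits badly with denominator a. The rule in section 4.3 against imputing missing data could lead an analyst there, but it does not say so. The reversal also needs early deaths in the comparison.

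Nor does any section say that a general linear model will be fitted to time to death. That is inferred from a footnote in a section headed as draft tables, while the body text of section 13 points to Cox. The row also matches no stand-alone outcome in section 5.2, so it may be a slip in the table shell.

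Reading B is not worthless either. With complete follow-up to a common horizon it is the restricted mean survival time. Differences in recruitment date should be balanced by randomisation; unequal loss to follow-up would remain a problem.

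Finally, an excess of deaths would not be hidden. The relative risk of death stands directly above, time to death is also a win-ratio component, and section 4.8 has a win-ratio sensitivity analysis that starts after 28 days.

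All of this stands, and it limits the consequence. It does not make the row right: Table 4 still conflicts with section 13, the value for survivors is still undefined, and the relative risk ignores when deaths occur.

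**Conclusion.** The point holds as a contradiction and an ambiguity. Table 4 assigns a censored outcome a mean difference and nowhere a hazard ratio, against the rule in section 13, and leaves survivors without a value or a censoring rule. Under the assumed rates the two readings give about +5.9 and -1.2 years from the same data. The size rests wholly on those rates, and the reversal on the dead-only reading with some early deaths. It should not be read as a claim that the plan commits itself to the misleading version, or that readers would have no other view of mortality. Severity is moderate: one secondary row in a draft table, with no primary result depending on it.

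**What to change.** Reconcile Table 4 with section 13:

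- Replace the footnote 3 row for time to death by a footnote 2 row: a Cox hazard ratio for all-cause death from randomisation, over everyone randomised (denominator a), with the living censored at the date last known alive. Add Kaplan-Meier curves by arm.
- Check proportionality, as section 13 already requires, and report the hazard ratio separately before and after 28 days, since early and late effects may differ. Note that the later ratio is conditional on survival to 28 days.
- If an effect in years is wanted, use the difference in restricted mean survival time to one stated horizon common to both arms.
- Drop the mean and SD for this outcome.

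The cost is one table row and a few sentences in section 13. No new data are needed, because the first step of the win ratio already requires survival times for the same people.

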**Table 5 Tertiary outcomes**

| Outcome                                               | Betamethasone
N = | Placebo
N = | Unadjusted
RR or mean
difference
(95% CI) | Adjusted RR or
mean difference
(95% CI) | P value |
|-------------------------------------------------------|----------------------|----------------|----------------------------------------------------|-----------------------------------------------|---------|
| Functional difficulties (n/N, %)          |                      |                |                                                    |                                               |         |
| Physical activity (categorical) (n/N, %)  |                      |                |                                                    |                                               |         |

|                                                                                                                                                 |  |  |  |  |  |
|-------------------------------------------------------------------------------------------------------------------------------------------------|--|--|--|--|--|
| Type 2 diabetes mellitus (n/N, %)                                                                                                   |  |  |  |  |  |
| Type 1 diabetes mellitus (n/N, %)                                                                                                   |  |  |  |  |  |
| Gestational diabetes mellitus (n/N, %)                                                                                              |  |  |  |  |  |
| Heart failure (n/N, %)                                                                                                              |  |  |  |  |  |
| Atrial fibrillation (n/N, %)                                                                                                        |  |  |  |  |  |
| Number of babies ≥20 weeks' gestation fathered
(median, 95% CI)                                                                  |  |  |  |  |  |
| Age at menarche (mean, SD)                                                                                                          |  |  |  |  |  |
| Proportion who have reached menopause (n/N, %)                                                                                      |  |  |  |  |  |
| Age at menopause (mean, SD)                                                                                                         |  |  |  |  |  |
| Need for assisted reproductive technology (n/N, %)                                                                                  |  |  |  |  |  |
| Polycystic ovarian syndrome (n/N, %)                                                                                                |  |  |  |  |  |
| Total number of pregnancies ≥20 weeks (parity)
(median, 95% CI)                                                                  |  |  |  |  |  |
| Diagnosis or treatment of a mental health disorder
(n/N, %)                                                                      |  |  |  |  |  |
| Depression (n/N, %)                                                                                                                 |  |  |  |  |  |
| Bipolar affective disorder (n/N, %)                                                                                                 |  |  |  |  |  |
| Anxiety disorder (n/N, %)                                                                                                           |  |  |  |  |  |
| Schizophrenia (n/N, %)                                                                                                              |  |  |  |  |  |
| Inpatient admission for a mental health disorder
(excluding mental disorders due to known physiological
conditions) (n/N, %)  |  |  |  |  |  |
| Prescriptions of pharmaceuticals for mental health
disorders (n/N, %)                                                            |  |  |  |  |  |
| Total number of fractures (median, 95% CI)                                                                                          |  |  |  |  |  |
| Cancer diagnosis (n/N, %)                                                                                                           |  |  |  |  |  |
| Allergic condition other than asthma (diagnosis of or
prescription of treatments for allergic conditions) (n/N,
%)            |  |  |  |  |  |
| Chronic kidney disease (n/N, %)                                                                                                     |  |  |  |  |  |
| Self-reported oral health (n/N, %)                                                                                                  |  |  |  |  |  |

|                                                                 |  |  |  |  |  |
|-----------------------------------------------------------------|--|--|--|--|--|
| Number of teeth removed for decay (median, 95% CI)  |  |  |  |  |  |
| Any court charges or convictions (n/N, %)           |  |  |  |  |  |
| Employment status (n/N, %)                          |  |  |  |  |  |
| Proportion with tertiary qualifications (n/N, %)    |  |  |  |  |  |
| No secondary school qualification (n/N, %)          |  |  |  |  |  |

Relative risk, Hazard ratio, Mean difference

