## 4. Methods for the ANCHOR Study: follow up of the Auckland Steroid Trial F1

### 4.1. Study design

This study consists of long term follow up of the Auckland Steroid Trial at 50 years comparing outcomes in offspring (F1) for those exposed to antenatal corticosteroid to those exposed to placebo.

Participants were blinded to allocation from randomisation up to 30-year follow up, at which point those participants who wished to have their treatment allocation disclosed were informed by letter. Investigators and all study staff for this 50-year follow up remained unaware of treatment allocation.

Follow up consists of a questionnaire based on the New Zealand Health Survey and consent to accessing routinely collected data from government agencies including the Ministry of Health (including Testsafe), Ministry of Education, New Zealand Qualifications Authority, Accident Compensation Corporation, Ministry of Justice and Statistics New Zealand.

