**Reproductive system outcomes: Female**

- Age at menarchecS
- Number who have reached menopause and age at menopausecS
- Need for assisted reproductive technologycS
- Polycystic ovarian syndromecS
- Total number of pregnancies  $\geq 20$  weeks (parity)cS

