#### 4.3. Approach for withdrawals, missing data and outliers

Data up to the point of withdrawal will be used for those participants who have withdrawn from the study unless they have withdrawn their consent for use of their data. No imputation will be performed for missing data. We do not plan to exclude outliers from the analysis. Sensitivity analyses will be performed to assess the impact of missing data on the primary and secondary outcomes.

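### Age at menopause is tested as a mean difference among women already menopausal at about 50, which biases the comparison toward zero; the Cox model already in the SAP would avoid this

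*SAP*

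**What the plan says.** Section 5.3 lists, under female reproductive outcomes, "Number who have reached menopause and age at menopause cS". The superscript c sets the denominator: "Denominator will be all participants who consented to this follow-up study with data available for the outcome".

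Table 5 splits this item into two rows. One is "Proportion who have reached menopause (n/N, %) 1", a relative risk. The other is "Age at menopause (mean, SD) 3". The legend reads "1 Relative risk, 2 Hazard ratio, 3 Mean difference", so the second row is a mean difference with a confidence interval and a P value. Section 13 gives the model: "For continuous outcomes, analysis will be by general linear modelling after assessing model assumptions", with an identity link and a normal distribution.

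The study design section describes "long term follow up of the Auckland Steroid Trial at 50 years". Under the heading on withdrawals, missing data and outliers, section 8 says "No imputation will be performed for missing data". It plans missing-data sensitivity analyses for primary and secondary outcomes only. No rule covers women who have not reached menopause when they answer the questionnaire.

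Elsewhere the SAP treats ages at an event differently. In Tables 3 and 4, age at (or time to) a first major adverse cardiovascular event, and ages at first myocardial infarction, stroke, heart failure admission and cardiovascular death, are all reported as hazard ratios. Section 13 assigns time-to-event analyses to a Cox model.

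**The concern.** Having a row for the proportion who have reached menopause shows that the plan expects some women not to have reached it. Those women have no age at menopause. With denominator c and no imputation they drop out of the mean, so women are selected into that row by the outcome being measured.

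The selection does not cancel between arms. If one arm has earlier menopause, more of its women fall below the cut-off, and the extra ones have ages just under it. They raise that arm's observed mean and pull the two means together. Checking the linear model's assumptions would not repair this, because the women above the cut-off are absent from the data being checked.

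The aim is to look for long-term effects, and the hypothesis is that there are no adverse ones. A bias toward zero favours that hypothesis. Readers could also see a relative risk pointing to earlier menopause beside a mean difference close to nil. Age at menarche, in the same table, does not have this problem, because it is complete by 50.

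**Working it through.** **The plan's own figures.** The SAP gives no sample size, power, mean or SD for this outcome, so there is nothing to reproduce.

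**Inputs.** From the SAP: total sample size 420 (section 9), two-sided 5% tests (section 13), follow-up at about 50 years (section 4.1). Assumed, and not in the SAP: half the participants are women and arms are equal, so 420 / 4 = 105 women per arm; age at menopause is Normal with mean 50–51 and SD 3–5; the true shift is 1–2 years earlier; follow-up is at exactly 50 or uniform over the ranges below.

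**Formulae.** For follow-up age F, mean μ and SD σ, let a = (F − μ)/σ and λ = φ(a)/Φ(a). Then:

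- proportion menopausal = Φ(a)
- observed mean = μ − σλ
- observed SD² = σ²(1 − aλ − λ²)

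**Worked case: F = 50, σ = 4, μ = 51 against 49.5.**

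1. Control arm: a = −0.25, φ = 0.3867, Φ = 0.4013. Mean = 51 − 4 × 0.3867/0.4013 = 47.15; SD 2.24.
2. Steroid arm: a = 0.125, φ = 0.3958, Φ = 0.5497. Mean = 49.5 − 4 × 0.3958/0.5497 = 46.62; SD 2.50.
3. Observed difference = 0.53 years. Share retained = 0.526/1.5 = 35%.
4. Women contributing: 105 × 0.4013 = 42.1 and 105 × 0.5497 = 57.7. SE = √(2.24²/42.1 + 2.50²/57.7) = 0.477, so z = 1.10 and power is about 20% by this approximation (17% simulated).
5. If every woman's age were known: SE = 4√(2/105) = 0.552, z = 2.72, power about 78%.

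**Across follow-up ages.** The first results column covers means 50–51, SD 3–5 and shifts of 1–2 years. The power columns use mean 51, SD 4, a 1.5-year shift and 105 women per arm.

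| Follow-up age | Shift retained | Planned mean difference | Log-rank, censored | Planned proportion RR |
|---|---|---|---|---|
| exactly 50 | 33–44% | 17% | 65% | 57% |
| 46–51 | 34–46% | 15% | 56% | 50% |
| 48–52 | 38–51% | 20% | 62% | 54% |
| 48–54 | 45–64% | 29% | 63% | 50% |
| 47–55 | 50–71% | 32% | 64% | 44% |

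Power is simulated, except the 48–54 entry in the last column. That entry follows from 50.0% against 63.4% menopausal: 1.96 × √(2 × 0.567 × 0.433/105) = 0.134, equal to the difference itself, so power is 50%. Allowing for variation between runs, the planned row's power is about 14–33%.

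For follow-up at 45–50 the share retained is 31–41%. There 20.6% and 31.9% are menopausal, the difference is 0.498 and the SE is √(2.22²/21.6 + 2.39²/33.5) = 0.631, so the planned row's power is about 12%, below the quoted range.

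**Under no effect**, the truncated t-test and the log-rank test both reject about 5% of the time. The fault is loss of a real difference, not false positives.

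**The case against.** A reader might infer that truncation always removes at least half of any true shift and most of the power. The documents do not support that. They give neither the ages at questionnaire nor a menopause-age distribution. At 47–55 the row keeps 50–71% of the shift. Over a wider grid (means 49–52, SD 3–5) with a 2-year shift and follow-up at 48–54, it keeps more than half of complete-data power in 8 of 12 settings.

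A reader might also infer that the trial would miss an effect on menopause altogether. It need not. The proportion row compares all women with data by randomised arm, is not truncated, and trails the log-rank test by only about 6–8 points at SD 4 when follow-up is at exactly 50, 46–51 or 48–52. The gap grows to 20 points at 47–55 (44% against 64%). That row ignores age at questionnaire, but with random allocation this is not a bias, and Table 2 reports age at follow-up by arm. Stripping it of its estimate and P value would be a preference, not a correction.

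The hazard-ratio footnote that no Table 5 row uses proves nothing about intent: similar legends recur under other tables, and all are headed as drafts.

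The outcome is tertiary, has no power claim, and the error is toward no difference with type I error held. All of this limits the importance of the point. It does not rescue the mean-difference row, which would still be published as an effect estimate with a P value although it is biased whenever there is an effect.

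**Conclusion.** The mean-difference row is the wrong analysis for an outcome that is incomplete at the time of follow-up. It is also out of line with how the SAP handles its other ages at an event. The direction, toward zero, holds in every setting examined. The size depends on assumptions outside the SAP: roughly 30–70% of a true 1–2 year shift is lost. In the mean 51, SD 4, 1.5-year case, with follow-up at 50 or within 46–55, power is about 14–33%, against 56–65% for a censored analysis of the same women.

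The loss belongs mainly to this one row. The planned relative risk, at 44–57%, recovers much of it. The point is minor, but the correction is specific and cheap.

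**What to change.** In section 5.3 and Table 5, make age at menopause a time-to-event outcome under the Cox model in section 13:

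- Event: reported age at menopause.
- Censoring: women not yet menopausal are censored at their age at questionnaire.
- Denominator: all women with menopause status and the relevant age available.
- Effect measure: hazard ratio (footnote 2), with hazard ratio added to the Table 5 column heads. Covariate adjustment, the clustering approach in the addendum and the proportionality check apply as for the other hazard-ratio outcomes.
- Keep the mean and SD among menopausal women as description only, labelled as such, with no effect estimate or P value.
- Keep the proportion row and its relative risk as planned.

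The data are already planned: menopause status, age at menopause and age at follow-up. How surgical menopause is dated belongs with the outcome definitions in supplement S1, which is not shown here, and the change does not depend on it. The cost is a few lines of SAP text and one table row, and readers get a hazard ratio in place of a difference in years.
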